### Statistical analysis

The proportion of participants with a diagnosis of paratyphoid fever (the attack rate) in each arm with 95% CI will be presented after window for primary endpoint evaluation (after challenge phase). The VE will be estimated by calculating the difference in attack rate in the comparator and in the SII-TCV(B) arm relative to the attack rate in the comparator arm, as seen below:

 VE=100×(AR_comparator_−AR_SII-TCV(B)_)/AR_comparator_=100×(1−AR_SII-TCV(B)_/ AR_comparator_)

Where VE is the VE and AR is the attack rate. The 95% CI of VE will also be calculated—if the lower boundary of the 95% CI is at or above 30%, the vaccine will be considered efficacious to protect against paratyphoid.

The immunogenicity data will be log-transformed prior to analysis to render a normal distribution, as data are expected to be highly skewed. Values below the limit of detection will be replaced by half the value of the lower limit before transformation. Primary analysis will be conducted on a per-protocol basis for all participants who received vaccination with no critical protocol deviation. A modified intention-to-treat analysis will also be conducted as a sensitivity analysis.^56^

The geometric mean concentration of antibodies will be calculated for each arm as the antilogarithm transformation of the mean of the log10 transformed concentration, with 95% CI calculated as the antilogarithm transformation of the lower and upper limits.

For the non-inferiority primary endpoint, the GMR will be calculated as antilogarithm of the difference between the mean of the log10 transformed concentration in the SII-TCV(B) and in the comparator arms. The 95% CI will be calculated as the antilogarithm transformation of the lower and upper limits. If the lower boundary of the 95% CI of the GMR is above 0.67,^54^ this bivalent vaccine will be considered non-inferior to the comparator Vi-PS.

Secondary analysis will use the Kaplan-Meier method to conduct time-to-event analyses, such as time to positive blood culture or time to oral temperature ≥38 ºC. Participants not meeting criteria for an individual component of the primary endpoint, or who withdrew or had potential interference with vaccine effect or infection challenge, will be censored in the analysis. Sensitivity analyses by sex and age and other variables will be added.

Exploratory objectives will aim to generate new hypotheses; thus, they will be analysed descriptively.

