## Study aims and objectives

This study aims to assess the efficacy of one dose of the bivalent conjugate vaccine candidate SII-TCV(B) against SPA in a CHIM, and to demonstrate non-inferiority of the immune response to the S. Typhi component compared with a UK-licensed typhoid vaccine. Secondary and exploratory objectives include characterisation of immune response to the vaccine and to the challenge, assessment of vaccine safety, and investigation of correlates of protection against SPA. Table 1 lists primary and secondary objectives and outcomes, with a complete list found in more detail in the online supplemental table S1.

**Table 1 T1:** Primary and secondary objectives and outcomes of the BiVISTA study

Study objectives	Outcome measures
Primary objectives	
To evaluate the efficacy of SII-TCV(B) against SPA compared with a licensed Vi polysaccharide vaccine in a healthy adult paratyphoid A challenge model	Proportion of participants developing S. Paratyphi A infection within 14 days following challenge, according to pre-specified diagnostic criteria
To evaluate the non-inferiority of the immune response to the *Salmonella* Typhi component of SII-TCV(B) compared with the licensed Vi Polysaccharide vaccine	Geometric mean concentration (GMC) of S. Typhi Vi antigen-specific IgG at day 28 following vaccination
Secondary objectives	
To evaluate the safety and tolerability of SII-TCV(B) compared with a licensed Vi polysaccharide vaccine	Occurrence of: local solicited events in 7 days following vaccination systemic solicited events in 7 days following vaccination unsolicited events in 28 days following vaccination serious adverse events following vaccination throughout study participation
To evaluate the immunogenicity of SII-TCV(B) compared with a licensed Vi polysaccharide vaccine	Quantification of S. Paratyphi A antigen-specific antibodies at 28 days following vaccination: GMCs, geometric mean fold rise (GMFR) and seroconversion (fourfold rise to prevaccination) for anti-LPS IgG, IgA and IgM and SBA titres Quantification of S. Typhi antigen-specific antibodies at 28 days following vaccination: GMCs, GMFR and seroconversion (four-fold rise to prevaccination) for anti-Vi IgG and IgA

BiVISTA, Bivalent Vaccination against *Salmonella* Typhi and SPA; SBA, serum bactericidal assay; SII-TCV(B), Serum Institute of India Typhoid Conjugate Vaccine (Bivalent); TCV, typhoid conjugate vaccine.

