The study is sponsored by the University of Oxford and will be conducted in 13 study centres (listed in the online supplemental material). All parent sites are equipped for safe participant review and adequate sample processing. Participants will be recruited, vaccinated and followed up at their parent site. Challenge agent administration will be centralised and conducted under predefined standard operating procedures. A study design diagram is presented in figure 1. Participants will be reimbursed for their time, travel and inconvenience.

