#### Randomisation

Participants will be randomised in a 1:1 ratio to receive a single intra-muscular dose of SII-TCV(B) or a Vi-PS (Typhim Vi). A randomisation list, generated by an OVG statistician using random block sizes (2 and 4), will be used to ensure equal target size in both arms. The randomisation will be stratified by parent site and uploaded to a web-based system (Research Electronic Data Capture, REDCap) that automates the allocation.

Unblinded clinical staff will run the randomisation on REDCap just before administering vaccine. The unblinded staff will not be involved in any postvaccination procedures and are independent from the blinded team.

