#### Laboratory testing

Samples collected for safety monitoring and microbiological endpoints will be processed and reported locally. For the primary and secondary endpoints, immunological assays to evaluate levels of anti-Vi and anti-LPS IgG, IgA and serum bactericidal assays will be validated and undertaken at an external laboratory. Exploratory endpoints will be undertaken at OVG. Blood sample collection and other samples timepoints are summarised in online supplemental table S7.

Participants will also be able to consent to transfer unused samples to the Oxford Vaccine Centre Biobank at the end of the study.

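### Both primary analyses are written as unadjusted two-arm comparisons, although randomisation is stratified by site and baseline anti-Vi IgG is collected: valid, but a small efficiency gain is left unused

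*Protocol article*

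**What the plan says.** Design (protocol article, Study design and Randomisation): the trial "will be conducted in 13 study centres". "Participants will be randomised in a 1:1 ratio", in blocks of 2 and 4, and "The randomisation will be stratified by parent site".

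Baseline (Table 1): the secondary typhoid endpoints include "GMCs, GMFR and seroconversion (four-fold rise to prevaccination) for anti-Vi IgG and IgA", so a pre-vaccination anti-Vi IgG value has to be measured.

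Analysis (Statistical analysis):
- Efficacy: "The VE will be estimated by calculating the difference in attack rate in the comparator and in the SII-TCV(B) arm", relative to the comparator rate. The claim is made if the lower 95% limit is at least 30%.
- Typhoid component: "the GMR will be calculated as antilogarithm of the difference between the mean of the log10 transformed concentration" in the two arms. Non-inferiority is claimed if the lower 95% limit exceeds 0.67.

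Neither estimator contains site or baseline. The only mention of covariates is a promise, placed with the secondary analyses, of sensitivity analyses by sex, age and unnamed other variables. The article does not name the interval method for VE.

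**The concern.** Each primary claim is decided by one confidence limit, so interval width matters.

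Blocking within site already balances the arms within each site. If sites differ in attack rate or antibody level, an unstratified standard error still counts that between-site variation, and the interval is wider than the design requires. Sites could differ in the efficacy endpoint because "Samples collected for safety monitoring and microbiological endpoints will be processed and reported locally".

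For the GMR, a baseline that predicts the day-28 value would remove part of the residual variance.

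At stake is a modest amount of power. It matters most for non-inferiority, where the stated assumptions leave little reserve above 90%, and for efficacy if true VE is below the design value.

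**Working it through.** **1. The plan's own figures (Sample size section).**

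Non-inferiority: margin 0.67, true GMR 1.2, log10 SDs 0.57 and 0.47, 5% attrition.
- n per arm = 192 × 0.95 / 2 = 91.2, taken as 91.
- SE = √((0.57² + 0.47²)/91) = √(0.5458/91) = 0.0774.
- Power = Φ(log10(1.2/0.67)/SE − 1.96) = Φ(0.2531/0.0774 − 1.96) = 90.5%.

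Efficacy: comparator rate 58%, vaccine rate 0.30 × 58% = 17.4%, null rate 0.70 × 58% = 40.6%. Fisher's exact test of 17.4% against 40.6% at 85 per arm has 90.0% power. That this was the method used is inferred.

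Both stated power targets are therefore met with no adjustment.

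**2. GMR adjusted for baseline.** SE² is multiplied by (1 − r²), where r is the correlation of log10 baseline with log10 day-28 anti-Vi IgG. The documents do not give r, so a range is shown.

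| r (assumed) | SE | Power at 91 per arm | n per arm for 90% |
|---|---|---|---|
| 0 | 0.0774 | 90.5% | 90 |
| 0.1 | 0.0771 | 90.7% | 89 |
| 0.2 | 0.0759 | 91.6% | 86 |
| 0.3 | 0.0739 | 92.9% | 82 |
| 0.5 | 0.0671 | 96.5% | 68 |

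If site alone explained 1%, 5% or 10% of the log10 variance (assumed), power would be 90.7%, 91.8% or 93.1%.

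The reserve is thin. At the 10% dropout used for efficacy (192 × 0.90 / 2 ≈ 86 per arm), unadjusted power is 88.8%; r = 0.2 would restore 90%.

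**3. VE stratified by site.** Simulation with 13 near-equal sites, 172 evaluable participants, 1:1 within site and a 58% comparator rate. The crude risk ratio with a log (Katz) interval is compared with the Mantel-Haenszel risk ratio (Greenland–Robins variance). The Katz interval and the between-site SDs of the logit attack rate are assumptions. Entries are the percentage of trials with a lower limit of at least 30%.

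| True VE | Site SD | Crude | Mantel-Haenszel |
|---|---|---|---|
| 70% | 0 | 96.9 | 96.9 |
| 70% | 0.5 | 96.7 | 96.8 |
| 70% | 1.0 | 96.9 | 97.3 |
| 70% | 1.5 | 96.5 | 97.3 |
| 60% | 1.0 | 78.0 | 80.2 |
| 60% | 1.5 | 79.1 | 82.6 |
| 55% | 0 | 60.8 | 60.5 |
| 55% | 0.5 | 61.1 | 61.6 |
| 55% | 1.0 | 60.3 | 63.2 |
| 55% | 1.5 | 60.9 | 66.2 |
| 30% (null) | 0 | 2.2 | 2.1 |
| 30% (null) | 1.0 | 1.5 | 1.9 |
| 30% (null) | 1.5 | 1.3 | 1.9 |

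The VE 70% rows use 15,000 replicates and the others 8,000. The Monte Carlo standard error near 60% is √(0.6 × 0.4/8000) ≈ 0.5 points. A 15,000-replicate repeat at VE 55% gave gains of 2.9 points (SD 1.0) and 5.7 points (SD 1.5).

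The 97% at VE 70% does not conflict with the stated 90%. Exact enumeration of the Katz-interval rule at 85 per arm gives 96.7%, so that rule has more power than the Fisher calculation.

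**4. Where the VE gain comes from.** The sampling SD of the log risk ratio is the same for both estimators: 0.265 and 0.265 at VE 70%, SD 1.0. What differs is the estimated standard error. At VE 30% and SD 1.0, the crude mean SE is 0.1656 against a true SD of 0.1571 (0.1656/0.1571 = 1.05, about 5% too wide). Mantel-Haenszel gives 0.1567 against 0.1569.

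**The case against.** The case for leaving the plan alone is substantial.

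- **Nothing is invalid.** The crude analyses do not inflate type I error. In the simulations crude VE interval coverage is about 95–97%, so at worst slightly conservative.
- **Sites may hardly differ.** Challenge is centralised under set procedures, with one strain, one dose range and common diagnostic criteria. The documents give no evidence of site variation in attack rate. A logit SD of 1.5 would mean comparator attack rates from about 7% to 96% across sites (logit 0.58 = 0.32, ± 1.96 × 1.5). The anti-Vi assay is also centralised, so laboratory differences should add little to the GMR variance.
- **VE 55% is not the design point for the 30% bound.** Table 3 claims 80% power there only against 19%.
- **The baseline may carry little information.** Eligibility excludes prior typhoid vaccination, prior enteric fever and long endemic residence, and values below detection are set to a constant. Many baselines could be nearly identical.
- **The true GMR is assumed to exceed 1.2**, so non-inferiority power may be above 90.5% anyway.
- **The interval method is not stated**, and the SAP, which is not shown, may set it.

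All of this stands, and it limits the size of the point. It does not remove it: the article does not merely omit adjustment but writes out two unadjusted estimators and ties the success rules to their intervals.

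A reader might infer that both primary analyses lose precision materially, or that the trial is underpowered because of this. The documents do not support either reading. The crude VE estimate is as precise as the stratified one, and the stated power is reached without adjustment.

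**Conclusion.** The point holds as a minor one, with moderate confidence. The plan stratifies by site and collects a relevant baseline, then specifies primary estimators that use neither.

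For the GMR, which is the main point, the direction of gain is clear but its size is not. It is 0.2 to 2.4 points of power for an assumed correlation of 0.1 to 0.3, and close to nothing if most baselines are below detection.

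For VE, the gain is in interval width only. It is under 1 point of power at VE 70%, and about 2 to 5 points at VE 55–60% if the site logit SD is 1.0 to 1.5 (5.7 at most, in the repeat run). There is essentially no loss if sites do not differ. Neither primary conclusion is threatened by the plan as written.

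**What to change.** **GMR.** Define the primary estimate as the antilog of the arm coefficient from a linear model of log10 day-28 anti-Vi IgG on arm, log10 pre-vaccination anti-Vi IgG and parent site, and compare its lower 95% limit with 0.67. With 13 sites this uses 15 parameters (intercept, arm, baseline, 12 site terms) out of about 182 observations. Keep the unadjusted GMR as supportive.

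**VE.** Define the primary estimate as one minus the Mantel-Haenszel risk ratio stratified by parent site, with Greenland–Robins variance, and apply the 30% rule to its lower limit. Sites will average about 172/26 ≈ 6.6 evaluable participants per arm, so state in advance how the smallest sites are pooled. Report crude VE as supportive.

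Both changes should be settled before unblinding. The cost is a few sentences in the analysis plan and a few lines of code; no new data and no change in sample size are needed.

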#### Challenge visit and challenge phase

At the challenge site, participants will be given a pre-treatment with sodium bicarbonate solution 1 min before being orally challenged with SPA (strain NVGH308) at the dose of 1–5×10^3^ CFU suspended in 30 mL of sodium bicarbonate on visit D0. Participants will fast for 90 min before and after challenge administration. They will be directly monitored for a minimum of 15 min, but they remain on site for 2 hours; if they vomit within 90 min of challenge administration, they will be withdrawn from the study and treated with antibiotics. During this observation, participants will be instructed and observed practising hand hygiene according to WHO’s guidance. They will be given access to an e-diary, where they will record solicited symptoms daily (as seen in online supplemental table S5) for 21 days, including twice-daily measured temperatures, and they may add any unsolicited symptoms and medications for 28 days.

Box 1 lists the prespecified criteria for diagnosis of paratyphoid infection: if presenting with at least one of them, participants will be considered susceptible to the disease, prompting antibiotic treatment. Recruited participants will be naïve to enteric fever, and baseline stool samples will be collected to ensure no SPA will be present prior to challenge. Since the UK is not endemic for enteric fever, and participants will not travel to endemic countries, we will assume that all SPA recovered from blood or stool culture will be the challenge strain.

Box 1Criteria for the diagnosis of paratyphoid A infectionParatyphoid A fever is diagnosed if any of the following applyA positive blood culture for SPA from 72 hours postchallenge.A positive blood culture for S. Paratyphi A within 72 hours postchallenge, with one or more signs/symptoms of paratyphoid A infection (such as recorded oral temperature ≥38.0^o^C).Persistent positive blood cultures (two or more blood cultures taken at least 4 hours apart) for S. Paratyphi A within 72 hours postchallenge.Oral temperature ≥38.0^o^C persisting for 12 hours or longer, not necessarily continuously.

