#### Antibiotics

Treatment will be given to all participants, either at the time of diagnosis or at day 14 postchallenge for those who did not reach preset criteria for diagnosis. Participants will be observed taking the first dose of antibiotic; subsequent doses of antibiotics will be taken by the participant at home, with compliance checked via e-diary. Other reasons for commencing antibiotics are listed in the online supplemental box S1.

A 14-day course of ciprofloxacin (500 mg two times per day) was the first-line antibiotic course used in previous paratyphoid fever CHIMs.^43 47 48^ However, due to potential risks associated with ciprofloxacin, highlighted by the Medicines and Healthcare products Regulatory Agency (MHRA) alert in 2024,^51^ alternative strategies to reduce exposure to this antibiotic were explored. According to the British Infection Association, both azithromycin and ciprofloxacin are recommended as optimal oral options to treat enteric fever.^52^ Evidence from enteric fever CHIMs indicates that ciprofloxacin outperforms azithromycin, with quicker clearance of fever and bacteraemia, as well as quicker symptom resolution,^53^ resulting in improved antibiotic tolerability and significantly fewer instances of antimicrobial switching (unpublished data). To leverage the rapid efficacy of ciprofloxacin while mitigating potential safety concerns and reducing exposure to it, a combination regimen of 4 days of ciprofloxacin (750 mg twice daily) followed by 10 days of azithromycin (1 g on the first day, 500 mg on following days) will be the first-line treatment in this trial.

Second-line or third-line courses of antimicrobials will be offered, should a participant develop intolerance to the first line. Online supplemental box S2 lists the alternatives. In case the participant requires intravenous antibiotics, ceftriaxone will be the choice.

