#### Challenge

Some participants may develop symptoms of paratyphoid fever during the challenge phase, and there is a potential risk of severe disease. To mitigate risks, common symptoms of enteric fever and its severity will be monitored closely during the challenge phase during visits and via an electronic diary (online supplemental table S5), and severe disease, as defined by prespecified criteria (see box 2), will be monitored. Additional to an in-clinic daily review, the study doctor will review blood results and e-diary entries every evening. Antibiotics will be initiated within 24 hours (typically much sooner) of diagnosis criteria being met or on day 14 postchallenge, whichever occurs first. Due to a mild-moderate symptom profile,^43 48 59^ most participants are expected to be diagnosed with the endpoint of positive blood cultures rather than as a result of persistent fever.

Box 2Adverse events for special consideration related to challenge and criteria for severe paratyphoid A diseaseAdverse events for special consideration related to challengeSevere paratyphoid A infection, as defined in the protocol:Oral temperature >40.0ºC.Systolic blood pressure <85 mm Hg.Significant lethargy or confusion.Gastrointestinal bleeding.Gastrointestinal perforation.Any grade 4 laboratory abnormality.Failure to clinically or bacteriologically cure a participant of paratyphoid A infection: defined as persistent clinical symptoms or persistent bacteraemia within 14 days of start of effective antimicrobial treatment.Progression to convalescent shedding of bacteria: defined as positive stool culture at least one week after completion of second course of antibiotics, in line with United Kingdom Health Security Agency (UKHSA) guidance.Progression to chronic carrier state: defined as positive stool culture at least one year following challenge.Relapse of paratyphoid A infection: defined as recurrence of confirmed paratyphoid A infection following successful treatment.Transmission of S. Paratyphi A to a contact of a participant.Adverse events requiring a physician visit or emergency department visit which, in the opinion of study staff, are related to the challenge with S. Paratyphi A.

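### Kaplan-Meier for single diagnostic components: if participants treated on another criterion are censored at treatment, component risks and the apparent effect on fever are modestly overstated

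*Protocol article*

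**What the plan says.** In the protocol article, Statistical analysis: "Secondary analysis will use the Kaplan-Meier method to conduct time-to-event analyses, such as time to positive blood culture or time to oral temperature" of 38 ºC or more. The censoring rule names two groups in one sentence. The first is "Participants not meeting criteria for an individual component of the primary endpoint"; the sentence continues "or who withdrew or had potential interference with vaccine effect or infection challenge, will be censored in the analysis". No censoring time is given for either group, and no competing-event method is mentioned.

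Under Challenge visit and challenge phase, on the Box 1 criteria: "if presenting with at least one of them, participants will be considered susceptible to the disease, prompting antibiotic treatment". The Antibiotics section times treatment "either at the time of diagnosis or at day 14 postchallenge for those who did not reach preset criteria for diagnosis". The Challenge paragraph under Safety and potential risks expects one route to dominate: "most participants are expected to be diagnosed with the endpoint of positive blood cultures rather than as a result of persistent fever".

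**The concern.** Kaplan-Meier treats a censored participant as having the same future risk as those still under observation. Here one component's event ends the natural course of another. A participant with a positive blood culture and no fever is given antibiotics, which makes a later fever less likely. If that participant is censored at that moment, the analysis stands in for them with those remaining at risk, who are mostly uninfected or not yet infected. Infection itself causes the censoring, so it is not independent of the outcome.

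The imbalance between arms follows from the attack rates: the arm with more infection loses more participants to this censoring. The component results describe what the vaccine prevents (bacteraemia, fever, or both), and any distortion would run in the vaccine's favour.

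**Working it through.** **Inputs from the article.** Comparator attack rate 58% (22/38 = 57.9%). SII-TCV(B) attack rate at a vaccine efficacy (VE) of 70%: 0.58 × (1 − 0.70) = 17.4%. Both reproduce. The article gives no figure for the Kaplan-Meier analyses.

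**How many are treated early.** 192/2 = 96 per arm; less 10% dropout, about 86.
- Comparator: 0.58 × 86 ≈ 50 diagnosed and treated before day 14.
- SII-TCV(B): 0.174 × 86 ≈ 15.

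**The mechanism by hand.** Suppose a share s of infected participants is treated on blood culture and censored before the fevers occur, and the observed fever-component VE is 70%. Dividing the fever count by those still at risk, rather than by all challenged, gives

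VE from 1−KM = 1 − 0.30 × (1 − 0.58s)/(1 − 0.174s).

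- s = 0: 70.0%
- s = 0.10: 1 − 0.30 × 0.942/0.9826 = 71.2%
- s = 0.25: 1 − 0.30 × 0.855/0.9565 = 73.2%
- s = 0.50: 1 − 0.30 × 0.710/0.913 = 76.7%

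If those participants are kept in the risk set to day 14, both denominators are the full arm and the answer is 70% for every s. The values of s are assumptions.

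**Simulation, large samples, censoring at antibiotic start.** Timings are assumed because the article gives none. Central case: bacteraemia around day 7 (SD 2), treatment 1 day later, 60% of infected febrile if untreated, fever on average 1 day after bacteraemia (SD 2); for blood culture, 10% of infected diagnosed by fever first. VE is from unrounded values.

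| Component, true VE | Incidence before treatment, comparator v vaccine | VE | 1−KM, comparator v vaccine | VE |
|---|---|---|---|---|
| Fever, 70% | 0.174 v 0.053 | 70% | 0.207 v 0.055 | 74% |
| Fever, 55% | 0.174 v 0.078 | 55% | 0.207 v 0.083 | 60% |
| Fever, 30% | 0.175 v 0.122 | 30% | 0.208 v 0.135 | 35% |
| Fever, 0% | 0.175 v 0.174 | 0% | 0.208 v 0.207 | 0% |
| Blood culture, 70% | 0.521 v 0.157 | 70% | 0.545 v 0.159 | 71% |

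In the comparator arm, fever risk without treatment is 0.342. So 1−KM at 0.207 is neither fever under the trial's policy (0.174) nor fever in untreated infection.

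**Range for fever at a true VE of 70%.**
- Varying the central case (40–80% febrile, fever 0–2 days after bacteraemia, treatment 0–1 day after it): 72–76%.
- Log-normal times with median bacteraemia on day 6 and fever on day 7 (SD 0.3–0.4 on the log scale, correlation 0.5–0.8, 60–100% febrile): 76–78% with no delay to treatment, 73–74% with a 1-day delay, 71–73% with a 2-day delay.

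The direction favours the vaccine throughout. The size shrinks as the interval from sampling to treatment lengthens, because more fevers are then observed before censoring.

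**The case against.** The strongest objection is that the decisive premise is not in the text. The article says these participants are censored, not when. Visits are daily to day 14 and diary temperatures are taken twice daily for 21 days, so holding treated non-events to day 14 is feasible, and then 1−KM equals the observed cumulative incidence. A censoring time is also something an article may leave to the analysis plan. This stands, and it makes the bias conditional. It does not dispose of the point: the article does fix the method and does place participants treated via another criterion under the same rule as withdrawals. The interference clause, and review for only 4 days after a diagnosis, make censoring at or soon after treatment a natural reading. That clause does not name antibiotics, however, so it cannot settle the matter.

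Second, the fever outcome analysed is a temperature of 38 ºC or more, whereas the Box 1 fever criterion requires persistence for 12 hours or longer. A single reading does not by itself start treatment. True, but a blood-culture diagnosis does, and it is the expected main route.

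Third, the distortion is small beside sampling error. With 16 v 5 fever events among 85 per arm, the risk ratio is 5/16 = 0.3125 and the SE of its log is √(1/5 − 1/85 + 1/16 − 1/85) = 0.489, so VE is 69% with a 95% CI of about 19% to 88%. This stands as a limit on importance. A systematic shift in one direction is still worth removing when removal is cheap.

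Fourth, a cause-specific comparison that censors at the competing event is a legitimate analysis. Agreed, provided it is labelled as such and its complement is not read as a risk.

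**Conclusion.** The point holds in conditional form. If participants treated via another Box 1 criterion are censored at diagnosis or antibiotic start, the censoring is informative and, when the vaccine works, more frequent in the comparator arm. One minus Kaplan-Meier then overstates component risk under the treatment policy and inflates a 70% effect on fever by roughly 2 to 8 points, with about 1 point for blood culture. These sizes rest on assumed timings and treatment delays and show direction and order of magnitude only. With no vaccine effect there is no differential bias, so no false signal is created.

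A reader might infer that the component comparisons are biased as written, that the inflation is one known number, or that the efficacy conclusion is at risk. The article supports none of these. It gives no censoring time, it gives no event timings from which a single figure could be derived, and its success rule rests on the 14-day attack rate for the composite diagnosis, which this censoring does not touch. The component time-to-event outcomes are secondary analyses, with no test or margin attached in the article.

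**What to change.** - Keep Kaplan-Meier for time to first meeting any Box 1 criterion, where diagnosis by any route is the event.
- For each single component, report Aalen–Johansen cumulative incidence to day 14 by arm, with diagnosis or antibiotic start via another criterion as a competing event. Genuine withdrawals remain censored.
- State the censoring time for each group in the rule, and say whether fevers recorded after antibiotics have started count.
- If a comparison that censors at treatment is also wanted, label it cause-specific and do not present 1−KM as a risk.

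The cost is wording in the analysis plan and standard code. It needs no new data, and it can be settled before unblinding, which follows the last participant's day 28 post-challenge visit. One small downside: component results will describe incidence under the policy of treating at diagnosis, not the course of untreated disease, and the report should say so.
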